##### Healthcare professional focus groups: design, sample, recruitment and data collection

General Practice, Radiology and FHRP Clinic staff will be invited to participate in focus groups 2 months after BC-Predict has stopped being provided in each location. The groups will examine how well prepared they and associated staff were for implementing BC-Predict, along with views on acceptability of BC-Predict and how its implementation could be facilitated when widely implemented. We will run a multidisciplinary focus group in each location (total sample = ~ 36). Focus groups will be audio recorded and transcribed verbatim. If a participant is unable to attend the focus group but would like to take part, they will be given the option to be interviewed face-to-face or over the phone.

The analysis of these data will also be used to generate a list of additional resources required and a quantitative estimate of the impact on resources such as staff time. The groups will also aim to estimate the approximate cost of providing the BC-Predict intervention. These estimates will inform the economic analyses.

#### Methods: data analysis

For both interviews and focus groups, data will be analysed using a manifest level approach to thematic analysis as the themes are likely to be predominately deductive. Thematic analysis seeks and reports the patterns inherent within the data collected. It is a common qualitative analysis method that results in a rich, complex, yet accessible account of the data [51]. Themes will be coded at the manifest (or explicit) level [52]. It will do so taking an essentialist approach, which means that we aim to report the experiences, meanings and the reality of the participants [53].

Coding will be conducted systematically and iteratively. Negative cases will be sought to test the emerging coding framework. Regular coding meetings will be held to refine the coding structure. Data will be coded by independent researchers to check reliability in qualitative methods and ensuring that the fit between data and analysis is maximised. Percentage agreement on presence will be calculated. Coding will continue until the team are satisfied that codes and themes adequately describe and capture the data. Data will be stored and organised within Nvivo software.

### Sub-study three: assessing feasibility of increasing screening interval for women at low risk

#### Objectives

To evaluate the impact of providing materials for women at low risk explaining that less frequent screening may provide a better balance of benefits and harms for them.

#### Background

Women at lower risk of breast cancer are likely to receive less benefit from the NHSBSP but are more likely to experience overdiagnosis and treatment for cancers that will not cause them harm if left untreated. In this sub-study, we have chosen the risk threshold of 1.5% or below in newly screened women over 10 years, as this is the average risk level for a 40-year old woman, who currently would not be screened for a further 10 years. (Note that in the rest of the PROCAS study, a threshold of 2% or below was used to indicate below-average risk [10], so we use the term “low” to distinguish this distinct threshold in the present research). PROCAS indicated that 13.5% of women screened have a 10-year breast cancer risk of less than 1.5% when assessed by Tyrer-Cuzick and mammographic density [10]. This group of women are at a lower risk of developing breast cancer and the tumours they develop are much more likely to be early stage and slow-growing [10, 12]. Existing data suggest that a risk stratified NHSBSP may not only be potentially cost-effective [11], but also that it may be potentially more cost-effective to delay screening in low-risk women by optimising the screen interval [54].

Nearly 90% of the population have indicated that “screening is almost always a good idea” [55] and many women would feel aggrieved if they felt they were being denied a service inequitably. Relatedly, attendance at screening provides reassurance and peace of mind [56], so a lack of screening may result in increased worry about breast cancer. However, this view may be partly due to a lack of general awareness of issues such as overdiagnosis [57]. Many national screening figures believe that less frequent screening for women at low risk may be an important component of risk-stratified screening. Further, our ongoing developmental work suggests that this idea is acceptable to many women, including women who have received a below-average risk estimates.

#### Methods: design, sample, recruitment and data collection

In the final 4 months of the 16-month period of implementation of risk estimation, we will extend the offer of risk provision to include information about how, for women at low risk of breast cancer delaying further NHSBSP for a further period of 5 years may provide a better balance of benefits and harms for them. This information will be presented to all women in East Lancashire and Oldham as part of the invitation process, and repeated for women at low risk (< 1.5% over 10 years) as part of their risk feedback letter and accompanying leaflet. Every woman identified as being at low risk will be asked to complete the online questionnaire assessing harms and benefits of BC-Predict at 6 months, in contrast to the main BC-Predict study, where only a sub-sample will be asked to complete this questionnaire.

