### Setting

Women will be recruited from seven sites within three NHS Breast screening programmes: three sites within the Greater Manchester programme (Withington Community Hospital, Oldham lntegrated Care Centre and the Trafford mobile screening van only), and two sites each based in the East Cheshire (Macclesfield District General Hospital and Stockport mobile breast screening van locations) and East Lancashire (Burnley General Hospital and East Lancashire mobile breast screening van locations) programmes. Women invited to screening in East Cheshire and Withington/Trafford in the first 8 months of the study will be offered BC-Predict and women in East Lancashire and Oldham offered screening as usual. After 8 months, BC-Predict will be offered to women in East Lancashire and Oldham, with women in Cheshire and Withington/Trafford offered screening as usual.

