### Procedure

Women being offered BC-Predict will be sent an invitation letter one to two working days after their breast screening invitation letter is sent. The BC-Predict invitation letter will be sent along with the participant information sheet and instructions directing prospective participants to the online risk assessment platform. Each invitation letter will include details of the participant’s “Date of first offered appointment”. This is the first breast screening appointment date that was offered to the participant. This date is of relevance because participants will be able to join the study either before the date of their first offered appointment or up to six-weeks after. After this time it will no longer be possible for them to login to the BC-Predict risk assessment platform. Prospective participants will be directed to telephone the study helpline if they have any questions, or if they require any further information prior to deciding whether or not to take part. The timeline from the participant perspective is shown in Fig. 1. An overview of data-flows is shown in Fig. 2.

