### Analysis plan and power calculations

#### Core outcomes

In total, approximately *n* = 18,700 women will be offered BC-Predict and *n* = 18,700 will be offered usual care NHSBSP over the total 16-month period. Based on the recruitment rate in PROCAS, *n* = 18,700 women being offered BC-Predict should result in 8000 women taking it up. The attendance rate to usual NHSBSP in Greater Manchester is 69% [5, 10].

Core outcomes will be compared for cohorts of women who are invited to BC-Predict and those who are invited to usual care (NHSBSP). Thus we will have in excess of 8000 participants in BC-Predict and NHSBSP groups for both comparisons: (a) within-site and (b) between sites over the same time period. The primary outcomes are binary. Logistic regression will be the primary statistical analysis method. We shall assess heterogeneity effects using interaction tests in the logistic regression, to examine differences in outcomes by time or location or screening type (prevalent v incident). Even in the presence of geographic or temporal heterogeneity of the effect, or of carryover effects continuing beyond the crossover period, we will still have sufficient data for a valid and fully powered comparison.

For core outcomes 1 and 2, we are interested in equivalence, in that we anticipate that invitation to BC-Predict will not substantially affect screening attendance. With 18,700 women in each group we will have in excess of 90% power to establish equivalence, defined as a 95%CI on the difference which does not exceed ±5% on the attendance rate at first offered appointment, if the latter is around 50% [37]. Similarly, we will have more than 90% power for the same comparison for eventual attendance within 180 days if the latter is around 70%.

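### The BC-Predict invitation changes in months 13-16 at East Lancashire and Oldham, yet those women are pooled with standard BC-Predict in the attendance equivalence comparison

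*Protocol article*

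**What the plan says.** Under Setting, the three East Lancashire and Oldham sites take over BC-Predict for the second half of the study: "After 8 months, BC-Predict will be offered to women in East Lancashire and Oldham". The other four sites then return to usual screening.

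Sub-study three (Methods: design, sample, recruitment and data collection) changes the offer partway through that second half: "In the final 4 months of the 16-month period of implementation of risk estimation, we will extend the offer of risk provision". The added content is that "for women at low risk of breast cancer delaying further NHSBSP for a further period of 5 years may provide a better balance". It is not limited to women found to be at low risk: "This information will be presented to all women in East Lancashire and Oldham as part of the invitation process". Low-risk women receive it again with their risk feedback.

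On timing, Procedure states: "Women being offered BC-Predict will be sent an invitation letter one to two working days after their breast screening invitation letter is sent". The message can therefore arrive before the first offered appointment.

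The analysis plan for core outcomes counts "approximately *n* = 18,700 women will be offered BC-Predict and *n* = 18,700 will be offered usual care NHSBSP over the total 16-month period" and compares the two invited cohorts. For attendance at the first offered appointment and within 180 days it says: "For core outcomes 1 and 2, we are interested in equivalence". Equivalence means a 95% confidence interval for the difference that stays within ±5 points. Interaction tests by time, location and screening type are planned. Nothing says whether women invited in months 13-16 belong to the primary attendance comparison or are to be shown separately.

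**The concern.** The protocol fixes the comparison population in one section and changes the intervention inside that population in another. Lower screening uptake is the first potential harm that it lists, and the equivalence test on attendance is how that harm is judged. If the delay message alters attendance at the current appointment, the pooled estimate describes neither version of the invitation. A fall limited to the last 4 months would be averaged with 12 months of standard BC-Predict, and in an equivalence test dilution favours a finding of no effect. Alternatively, part of a pooled fall would be charged to standard BC-Predict.

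The change also falls in only one of the two site sequences, so the counterbalanced design no longer compares the same intervention in both. Sub-study three itself treats the versions as distinct: its intention outcome is compared with women recruited in the previous 12 months. The main analysis makes no such distinction.

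**Working it through.** **1. The plan's own figure.** Inputs from the core-outcomes power section: 18,700 per group, margin m = 0.05, attendance about 50% or 70%. The true difference is taken as zero and observations as independent.

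Power = 2Φ(m/SE − 1.96) − 1, with SE = √(2p(1−p)/18,700).
- p = 0.5: SE = 0.0052, half-width 1.96 × 0.0052 = 1.0 point, power >99.9%.
- p = 0.7: SE = 0.0047, power >99.9%.

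The stated power of more than 90% is reproduced; 2,599 or 2,184 per group would be enough for 90%.

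**2. Share of the arm that gets the message.** Site volumes are not given, so there are two assumptions.
- Equal sites: 3/7 × 4/8 = 21.4%, about 4,007 women.
- Equal BC-Predict numbers in the two 8-month periods: 1/2 × 4/8 = 25%, about 4,675 women.

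**3. What pooling does to an assumed effect.** Pooled shift = share × fall among exposed women. The falls are assumptions; the documents give none. The last two columns are the chance of still declaring equivalence at 50% attendance if standard BC-Predict has no effect.

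| Assumed fall | Shift, 21.4% share | Shift, 25% share | Declared, 21.4% | Declared, 25% |
|---|---|---|---|---|
| 5 points | 1.1 | 1.25 | ~100% | ~100% |
| 10 points | 2.1 | 2.5 | >99.9% | 99.8% |
| 15 points | 3.2 | 3.75 | 93% | 68% |
| 20 points | 4.3 | 5.0 | 28% | 2.5% |

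Within East Lancashire and Oldham the dilution is one half, so a 10-point fall moves the within-site estimate by 5 points.

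**4. Can the two versions be separated?** Let A be the four first-period sites and B the other three. Periods are months 1-8, 9-12 and 13-16. With equal site flow, 37,400 women over 112 site-months is 333.9 per site-month, which gives these cells:
- A1 10,686; A2 5,343; A3 5,343
- B1 8,014; B2 4,007; B3 4,007

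Under site and period terms with one effect per version (shown on the difference scale, with cell labels standing for attendance proportions):
- Standard BC-Predict = ½[(A1 − B1) − (A2 − B2)]. SE at 50% = √{(0.25/4)(1/10,686 + 1/8,014 + 1/5,343 + 1/4,007)} = 0.0064. The half-width is 1.25 points and equivalence power >99.9%.
- BC-Predict plus delay information, against usual care = ½[(A1 − B1) + (A2 − B2)] − (A3 − B3). SE = √{0.0064² + 0.25(1/5,343 + 1/4,007)} = 0.0123. The half-width is 2.4 points and equivalence power about 97%.
- Effect of the message itself = (B3 − A3) − (B2 − A2). SE = √{0.25 × 2 × (1/5,343 + 1/4,007)} = 0.0148, about 1.5 points.

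The design can therefore estimate both versions, provided that attendance would otherwise have moved in parallel in the two site groups.

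**5. Why plain exclusion is not the answer.** Over the full study both arms take 32 of 56 site-months (57%) from the A sites. Dropping months 13-16 from both arms leaves BC-Predict with 32/44 = 73% and usual care with 16/40 = 40%. If attendance differed by 10 points between site groups, an unadjusted comparison would be biased by (0.73 − 0.40) × 10 = 3.3 points, more than the 2.1-2.5 points at issue.

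**6. Self-reported outcomes.** These are sized at 527 per group for 90% power at d = 0.2: Φ(0.2√(527/2) − 1.96) = 0.90. Losing a quarter leaves 395 per group: Φ(0.2√(395/2) − 1.96) = 0.80.

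**The case against.** The strongest reply is that the message is about later rounds. It speaks of delaying further screening, the sub-study's outcome is intention to attend in 3 years, and women learn their risk only after a clear mammogram or after the six-week window. A reader might infer that the message acts directly on the attendance outcome; the documents do not show that. Spillover to the current appointment is plausible and no more.

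Large falls are also hard to support. Sub-study three's background puts 13.5% of screened women below the 1.5% risk threshold. If that share held among invitees and every such woman who would have attended stayed away, the fall would be 13.5% × 50% to 70%, or about 7 to 9 points, and 1.4 to 2.4 points pooled. Women do not know their risk at invitation, so this is an illustration and not a bound.

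A reader might also infer that the message cannot be told apart from site and calendar time. That is too strong: months 9-12 at the same sites and the concurrent usual-care sites give the contrast in step 4. The protocol already plans time and location interaction tests and will record changes in procedure.

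What stands is that no cut at month 12 is named, and a non-significant interaction would not turn a mixed estimate into an estimate for one intervention. A finer time cut could be left to an analysis plan. The comparison population could not, because the protocol itself sets it as everyone invited over 16 months.

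**Conclusion.** The point holds as a matter of what the primary estimate means. Followed as written, the plan mixes two versions of the invitation in about 21-25% of the BC-Predict arm, on the outcome used to judge the main screening harm, and dilution favours declaring equivalence. The share rests on even invitation flow.

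The consequence for attendance is conditional, since neither the size nor the direction of any effect is in the documents. A 10-point fall, twice the margin, would almost always be hidden, but that fall is an assumption. The stated power is not in doubt. All precision figures ignore clustering by site.

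**What to change.** In the core-outcomes analysis section:
- Keep all women and all months. Fit the logistic regression with site terms, calendar-period terms cut at months 8 and 12, and separate terms for standard BC-Predict and for BC-Predict plus delay information. Express the results as differences in attendance, the scale of the margin.
- Judge equivalence on the standard BC-Predict estimate.
- Report the months 13-16 version separately, stating the parallel-trends assumption.
- Give the pooled all-months result as a sensitivity analysis.
- Do not simply drop months 13-16 without site and period adjustment.

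For the self-reported outcomes, keep all women in the primary analysis and add a sensitivity analysis by message exposure. Excluding a quarter would cut power from 90% to about 80%, if sampling is spread evenly over the months.

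Cost: mainly wording. The attendance half-width goes from about 1.0 to about 1.25 points at 50% attendance, and power remains well above 90% under independence. Usual-care outcomes arrive in aggregated form, so the screening services must supply counts by site and by the three periods. The planned time and location interactions already need most of that breakdown; the cut at month 12 is the addition.

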A final important group of possible drawbacks of implementing risk stratification are the potential costs, both personal and financial, to implementing the communication of risk information on such a scale, including increased NHS staff workload and additional healthcare resources. Evidence is therefore required about the key drivers of the relative cost-effectiveness of communicating breast cancer risk estimates compared with current NHSBSP practice, understanding the key uncertainties in the current evidence base and potential value of future research [19]. Overall, it is imperative in order to highlight whether risk stratified screening will induce harms and if so, how they can be mitigated so as not to outweigh benefits, and allow more effective use of healthcare resources.

We have developed an automated system (BC-Predict) for offering an assessment of breast cancer risk to women when they receive their NHSBSP invitation, and generating letters to feedback this risk to women and relevant healthcare professionals. A development phase involved working with healthcare professionals that ensured that the care pathways were workable, and that informatics procedures functioned as intended. The patient information materials were co-produced with women who would be eligible for BC-Predict to promote good understanding and informed choices, and also minimise harms such as unnecessary worry.

In BC-Predict, risk estimation can be offered in real-time to women invited for breast screening via an online web system to allow consent and self-report measures to be provided. Risk assessment is based on self-report questions and breast density estimates automatically derived from mammography, and can also incorporate information from currently known breast cancer Single Nucleotide Polymorphisms (SNPs), derived from DNA contained in saliva samples. Women who receive a clear mammogram result are then sent a letter providing their 10-year breast cancer risk within 6 to 8 weeks after their mammogram. Thus all women will know their risks. Those women at moderate (> 5% but < 8% 10-year risk) or high (≥8% 10-year) risk are encouraged to attend a consultation at a FHRP Clinic, to discuss the offer of more frequent screening and chemoprevention.

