All BC-Predict participants will have been invited for breast screening but a proportion may choose not to attend their breast screening appointment; attendance at breast screening mammogram is not a compulsory part of the study. The Participant Information Sheet explains that participants’ mammographic breast density will be included in their risk assessment, providing they attend their mammogram within 6-weeks of their first offered appointment. It is also explained that including mammographic density increases accuracy of the risk assessment. Any participant who declines a mammogram or has a mammogram after this time will not have this data included in their risk assessment, which is explained in their risk feedback letter.

To assess self-reported harms and benefits, and to inform an economic analysis, a randomly selected subsample of *n* = 2108 women (*n* = 1054 each from usual care NHSBSP and BC-Predict) will be asked to complete questionnaires assessing psychological benefits and harms of BC-Predict at baseline, 3-months and 6-months. For women in both groups, the request to complete the questionnaire will be sent shortly after their mammography invitation but before their first offered mammogram appointment, asking for their help in evaluating a new approach to providing NHS breast screening. They will be given instructions to complete an online consent form and questionnaire using their unique study identification number on SmartSurvey (https://www.smartsurvey.co.uk/). The same women will be asked to complete the questionnaire three and 6 months after their first offered mammogram appointment. Women in both experimental groups will only receive follow-up questionnaires once they receive a clear mammogram result.

The risk assessment and feedback will take account of each patients’ journey through the NHSBSP. The study team will periodically check screening outcomes for participants. There are a number of initial screening outcomes: (a) clear mammogram and woman will be invited for routine breast screening in three-years (routine recall); (b) mammogram taken is technically inadequate so repeat mammogram is required (technical recall); (c): suspicious mammogram and further assessment required (recall for assessment). For all scenarios the GP will be informed of the participant’s involvement in the study and provided with their risk feedback.

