Participants who are confirmed as having a routine recall screening outcome will receive their risk feedback after this, approximately 6 weeks after their mammogram. Participants who are invited for a technical recall/recall for assessment appointment, and attend this appointment within 6 months of their first scheduled technical recall/recall for assessment appointment, and who are subsequently confirmed as not having breast cancer will receive a risk feedback letter following confirmation of an absence of breast cancer. Participants who are invited for a technical recall or recall for assessment appointment but do not attend within 6 months of the first scheduled technical recall/recall for assessment appointment (i.e. those for whom there is no screening outcome within 6 months of initial screening outcome) will receive their risk feedback 6 months after joining BC-Predict.

Participants who do not attend a breast screening appointment within six-weeks of their first offered breast screening appointment will receive their risk feedback after this six-week period (i.e. 7 to 8 weeks since their first offered breast screening appointment).

Participants who are diagnosed with breast cancer will not receive a standard risk feedback letter. Participants will be sent a letter 1 year after diagnosis which will offer them feedback from the study. If they opt to receive this, they will be sent a personalised letter explaining their breast cancer risk factors.

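### As written, the sub-study three message about delaying screening goes into the personal letters of low-risk women whose current screening episode is still incomplete (minor participant-safety point)

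*Protocol article*

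**What the plan says.** Sub-study three (Methods: design, sample, recruitment and data collection) runs in the last 4 of the 16 months in East Lancashire and Oldham. All women invited there get general information that, for those at low risk, waiting a further 5 years may give a better balance of benefits and harms. The information is then "repeated for women at low risk (< 1.5% over 10 years) as part of their risk feedback letter and accompanying leaflet". The sub-study's data-analysis section describes the message as a recommendation.

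The Procedure section sets out who gets a risk feedback letter. Besides women with routine recall and women cleared after recall, two other groups receive one:

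- Women who do not attend a technical recall or recall for assessment within 6 months: where "there is no screening outcome within 6 months of initial screening outcome) will receive their risk feedback 6 months after joining BC-Predict".
- Women not screened in time: "Participants who do not attend a breast screening appointment within six-weeks of their first offered breast screening appointment will receive their risk feedback", at 7 to 8 weeks after that appointment.

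The one exception is stated as: "Participants who are diagnosed with breast cancer will not receive a standard risk feedback letter". On how risk is estimated without a timely mammogram, the same section says: "Any participant who declines a mammogram or has a mammogram after this time will not have this data included in their risk assessment".

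**The concern.** The two rules are written separately and nothing links them. One makes the delay message depend on risk alone. The other sends letters to women who have not finished the current screen. Together they put the message into letters where it does not belong.

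The case that matters most is an unattended recall for assessment, which the Procedure section defines as following a suspicious mammogram. The stated inputs to the risk estimate are the questionnaire and breast density, not the suspicious finding, so such a woman can still fall below 1.5%.

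A non-attender can also still come to screening in this round. She could read a personal low-risk letter about delay as applying now. Her estimate omits density.

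**Working it through.** The plan gives no figure for this point, so the main check is a trace of the stated rules.

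**Rule trace for a sub-study woman with 10-year risk below 1.5%**

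| Status in the current episode | Risk letter (Procedure) | Delay message (sub-study three) | Episode complete? |
|---|---|---|---|
| Routine recall | Yes, about 6 weeks after mammogram | Yes | Yes |
| Recalled, confirmed cancer-free | Yes, after confirmation | Yes | Yes |
| Technical recall or recall for assessment not attended within 6 months | Yes, 6 months after joining | Yes | **No** |
| Not attended within six weeks of first offered appointment | Yes, at 7 to 8 weeks | Yes, on an estimate without density | **No** |
| Breast cancer diagnosed | No standard letter | No | Not applicable |

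Two groups with an incomplete episode receive the message.

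**Can a non-attender still attend when the letter arrives?** Core outcome 2 counts attendance up to 180 days from episode opening. The letter goes out at most 8 × 7 = 56 days after the first offered appointment. The window is still open unless more than 180 − 56 = 124 days separate episode opening from that appointment; the article does not state this interval. The power section plans on about 50% attending the first offered appointment and about 70% within 180 days. That is 70 − 50 = 20 points of later attendance, or 20/50 = 40% of those who miss the first date. These rates are for invitees. How many of the later attenders come after six weeks, and how many joined BC-Predict, is not stated.

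**Rough size.** Inputs: 8,000 expected joiners (Analysis plan, core outcomes); 3 of 7 sites, each open to BC-Predict for 8 months, with the sub-study in the last 4 (Setting, Participants, sub-study three); 13.5% below 1.5% (sub-study three, Background).

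- Scaling by sites: 8,000 × 3/7 × 4/8 = 1,714 joiners; × 0.135 = 231 low-risk women.
- Even monthly recruitment: 8,000 × 4/16 = 2,000 joiners; × 0.135 = 270 low-risk women.
- Each 1% without a completed episode: 2.3 to 2.7 letters.
- Assumed 1–10% incomplete: 231 × 0.01 = 2.3 up to 270 × 0.10 = 27 letters.

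The 1–10% is an assumption with no source in the document. The 13.5% comes from screened women assessed with density, so it need not hold for non-attenders.

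**The case against.** The strongest reply is that this is a condensed article. Conditional paragraphs in a letter template are the kind of detail left to the full protocol and the participant materials, and a safeguard may exist there.

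The article's wording also suggests that the message was meant for women who have finished the current screen:

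- The threshold is justified for newly screened women, the message concerns further screening, and the outcome is intention for 3 years ahead.
- The Background describes the usual route this way: "Women who receive a clear mammogram result are then sent a letter providing their 10-year breast cancer risk".
- Follow-up questionnaires go only to women with a clear mammogram, yet every low-risk woman is to be asked for the 6-month questionnaire. This fits a sub-study group that has had a clear result.

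There are mitigations too. The letter tells women when density was left out, the leaflet covers signs and symptoms, and "For all scenarios the GP will be informed". All invitees at these sites see the general information anyway. Nothing withdraws an outstanding recall.

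Much of this stands, and it keeps the point small. It does not remove it. The cues show likely intent, but none is a condition on who gets the message, and the Procedure section expressly adds letters without a clear mammogram. Even if newly screened were read as eligibility, a woman with an unattended recall has been screened. The questionnaire condition is written for questionnaires, not for letters. This is therefore more than missing detail: two explicit rules, followed as stated, produce the result.

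**Conclusion.** The point holds as a minor participant-safety matter. On the article's own rules, low-risk women with an unattended recall, and low-risk women not yet screened, receive the delay message in a personal letter; a cancer diagnosis is the only exception. Few women are likely to be affected: 2 to 27 if 1–10% of the 231 to 270 expected low-risk women have an incomplete episode. That share is assumed, and the true number cannot be derived. If newly screened means first screens only, 231 to 270 is too high, because the 8,000 joiners include incident screens. Bias in the attendance equivalence result or in the sub-study's comparison of intentions is not shown, and women are not told to skip the current episode.

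**What to change.** Put the delay message in the feedback letter and leaflet only when the current episode has ended in routine recall or a confirmed cancer-free outcome. Send other low-risk women the standard risk letter without it, and remind those with an outstanding recall to attend. The general information at invitation can stay; the change stops it being tied to a personal low-risk result before the episode is complete.

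The cost is one condition in letter generation and one sentence in the protocol. The data are already to hand: "The study team will periodically check screening outcomes for participants". The downside is slightly fewer recipients of the message. If the letter templates already apply this condition, stating it in the protocol is enough.
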